**Fig. 3 Fig3:**
[figure not shown]
Progression of activity completion (top row) and time epoch (below) on the watch face. Note, only the intervention group will see activity feedback

Each bar of the activity tracker fills as the patient meets a particular percentage of their target activity in the particular epoch. These are set to 1/3, 2/3 and 3/3 of the target such that the next bar (from red to green) will light up when the patient passes these markers. The full green bar lights up when the patient has met or exceeded their target. (See Fig. 4) The feedback page is only shown to the feedback group during the active time periods. At all other times, and at all times for the non-feedback group, the screen simply shows a larger version of the clock icon.

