### Design

This study is an efficacy, single-blind, randomized controlled trial with the assessor blinded to the group allocation. Participants cannot be blinded to group allocation and ward staff will not be. The intervention being studied is for all patients to wear a Smart watch throughout a normal working day (0800–1700 hours) from Monday to Friday for up to 15 days. They will be randomly assigned, using concealed allocation, to one of two groups where the watch gives:Feedback on amount of physical activity (movement) undertaken, two hourly for the first 8 hours and then for the last 1–2 hours (dependent on the battery life) orNo feedback about the physical activity levels during a 3-week intervention period.

All other interventions (medication, physical therapy) will be kept to their normal routine.

The flow of the study is shown in Fig. 1. Patients will be recruited from all admissions to the rehabilitation wards in the Second Affiliated Hospital of Anhui University of Traditional Chinese Medicine, a large urban hospital. Only patients admitted for rehabilitation after a recent stroke will be approached. The procedure used needs to be compatible with normal clinical practice.

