Participants will be randomly assigned to one of two groups: (1) feedback of activity levels; or (2) no feedback of activity levels (i.e. control group). A block stratified randomization approach with two strata will be used, based on walking speed at the time of recruitment. A threshold of 0.42 m/s [12] will be used to define two groups: slow walkers (< 0.42 m/s) unlikely to walk in the community, and moderate-fast walkers (> 0.42 m/s). People unable to walk at the time of recruitment will be classified as slow walkers. The block size will be 5.

Once recruited, the recruiting doctor will inform the research office personnel, who are not blinded, and they will then undertake allocation. Allocation will be performed using a computer program in Microsoft Excel to allocate groups and generate numbers for each stratum (slow walkers or not slow walkers); the allocation will be made by the research office staff after registration. The research office will then notify the ward about the patient’s allocation by telephone. The researchers who will be performing all assessments will remain blinded to group assignment throughout the study.

The participants’ rehabilitation programmes will continue as normal, with no change in relation to this study. Therapists will not specifically be informed about a participant’s group, but may learn this. However therapists will not specifically encourage use of the feedback (or the opposite).

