#### Intervention - the China Monitoring (CHMON) feedback system

The CHMON system utilized for the project is a ZGPAX S8 [13]. The S8 is a full android Smart watch encapsulated in a wrist-wearable unit. As such it is capable of running apps written for it and operating in a stand-alone manner. The hardware specifications for the ZGPAX S8 are shown in Table 1.

**Table 1 Tab1:** Hardware specifications for the ZGPAX S8 android Smart watch

	Hardware specification
Size	58 × 42.5 × 13 mm
Weight	67 g
Screen	40 mm capacitive touchscreen
Battery	3.7 V/470mAh Li-ion (rechargeable)
CPU	MTK6572 Dual Core 1.2 GHz
Memory	12 GB total
RAM	512 MB
Android version	4.4.2
Sensors	GPS, accelerometer
Connectivity	WiFi, Bluetooth, 2G, 3G
Waterproof	No

*CPU* central processing unit, *RAM* random access memory

The CHMON system is used both as a data gathering platform and as a feedback device to the patient in the experimental group (Fig. 2). The patient wears the device for 9 hours a day. In the intervention group, the watch will divide elapsed time into four periods of 2 hours, and one of 1 hour. In the control group the activity level is simply recorded, and no further processing occurs.

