**Fig. 4 Fig4:**
[figure not shown]
Standard protocol items: recommendation for interventional trials (SPIRIT) figure of study timing and activities. ADL, activities of daily living; WHO, World Health Organization

The first day will serve as a baseline measure, in which none of the participants will receive feedback on their activity levels. Thereafter each morning, an investigator will provide the participant with a Smart watch to be worn on the unaffected side and will remind the participant about the purpose of the watch; either to record activity (control group) or to provide feedback on activity (intervention group). Each evening an investigator will see the person, check that there have been no unexpected events or problems such as falls, or other adverse events, and then take the watch away so that data can be downloaded, and the watch recharged for use the next day.

In order to ensure that all researchers administer the intervention in a consistent manner, we will host a series of in-service training sessions on the use of the Smart watch. These in-services will focus specifically on the setup, data storage, and output from the CHMON system.

The control group will wear the same watch, and be seen each day by the researcher to collect the watch. In this way we will control for additional attention, and to an extent for any expectations generated by involvement in a trial and wearing a watch.

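### The watch face shows the allocation during wearing hours, and nothing in the article hides it at the face-to-face end-of-intervention assessment, so assessor blinding is not secured at that visit

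*Protocol article*

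**What the plan says.** On the display, the section on the CHMON feedback system (Methods) states: "The feedback page is only shown to the feedback group during the active time periods". It continues: "At all other times, and at all times for the non-feedback group, the screen simply shows a larger version of the clock icon". The legend to Fig. 2 describes the feedback as red-green bars that only one group sees.

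On wear, the Design section has all patients "wear a Smart watch throughout a normal working day (0800–1700 hours) from Monday to Friday for up to 15 days". The CHMON section adds: "The patient wears the device for 9 hours a day". For participants who get feedback, it specifies how the day is split: "the watch will divide elapsed time into four periods of 2 hours, and one of 1 hour". There is one exception: "The first day will serve as a baseline measure, in which none of the participants will receive feedback on their activity levels". The only removal described is in the evening, when an investigator will "take the watch away so that data can be downloaded, and the watch recharged for use the next day".

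On blinding, the randomization paragraphs of the Design section state: "The researchers who will be performing all assessments will remain blinded to group assignment throughout the study". The Abstract, the opening of the Design section and the Data collected section make the same claim. None of them qualifies it by visit or says how it is protected from the visible screen.

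**The concern.** The device that delivers the intervention also displays the allocation, and it sits on the wrist of the unaffected arm. The end-of-intervention battery in the Data collected section includes grip strength and a 10-metre walk, which need the participant and assessor in the same place. The gait test may even be done with a researcher supporting the participant. If the watch is on and lit at that moment, a glance reveals the group.

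At stake are the clinical outcomes that an assessor scores, prompts or encourages. They bear on the article's second hypothesis, that more activity leads to better mobility and possibly better cognition, arm function and independence. An assessor who knows the group may, without intending to, score or encourage in the direction of that hypothesis. This route is distinct from the question of who the assessor is: an assessor brought in from outside the ward could read the wrist just as easily.

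**Working it through.** There is no planned figure to reproduce. The check sets the statements side by side, with one piece of arithmetic.

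**1. Does the display differ by arm?** Yes. The feedback arm sees bars during active periods; controls see only the clock at all times (CHMON section and Fig. 2 legend).

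**2. For how much of the wearing day?**
- Wear time (Design): 0800 to 1700 = 9 h.
- Feedback periods (CHMON section): 4 × 2 h + 1 × 1 h = 9 h.
- Overlap: 9 / 9, the whole wearing day, if the active periods are these five periods.

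The Design section makes the length of the last period depend on battery life, so the end of the day is less certain. No statement says whether the screen stays lit between glances.

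**3. Is the display the same in both arms at any time of wear?** On Day 1 only, because no participant receives feedback then. From Day 2 no matching period is planned.

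**4. Is the watch off at the end-of-intervention assessment?** Not stated. The Abstract places the assessment at 3 weeks or discharge, whichever is sooner, without a time of day. The only removal described is in the evening. Two statements make daytime assessment likely without establishing it. The Discussion says ward doctors collected the clinical data within their routine duties. The Data collected section has research doctors ask about problems with the watch and look for a rash at every contact, which directs attention to the wrist.

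**5. Which results can this route reach?**

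| Item | Reached? | Reason |
|---|---|---|
| Daily activity score (primary) | No | Recorded by the device |
| Baseline assessment | No | No feedback shown in either arm |
| 12-week contact | No | By telephone |
| Watch compliance, length of stay | No | No rater needed |
| Rivermead Mobility Index | Little | 14 of 15 items are self-reported, 1 observed |
| WHODAS, EuroQol, Fatigue Severity Scale | Little | Questionnaires; participants are openly unblinded, so masking the watch would not remove self-report bias |
| Barthel, MoCA, grip strength, 10-metre walk at 3 weeks or discharge | Yes, if the watch is worn and visible | Rated, prompted or encouraged by the assessor |

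Grip strength is not in the list of measures compared between groups under Data handling and analysis. Nor is the 10-metre walk, although the Abstract names walking time as a measure of mobility. Both are collected at this visit, and the mixed-model paragraph says each outcome measure will be analysed.

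**6. What would masking by removal cost in data?** Each hour off the wrist is 1 / 9 = 11% of that day's wear, and 1 / (15 × 9) = 1 / 135 = 0.7% of the maximum wear over 15 days.

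**The case against.** The strongest reply is that this rests on silence in a condensed article. Whether a watch comes off before a grip or walk test is the kind of detail an assessor manual holds. The full protocol is not shown, and the timing figure is missing from the text. The article does say that assessors will not know the group, and an unstated safeguard does not contradict that. The assessment could also follow the last evening collection, in which case no assessor would see a lit watch. Finally, continuous display is one reading: the Background speaks of feedback at fixed time points, and the active periods are not defined where the term is used.

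Much of this stands. A reader might infer that every end-of-intervention assessor is unblinded, or that all assessments made between 0800 and 1700 on a wearing day are exposed. The documents do not support either as fact. They do not give the time of the assessment, whether the watch is on, or how many assessments fell in wearing hours. A figure of 100% would be only an upper bound that assumes the point in question. Nor is there support for extending the concern to the primary outcome or to every secondary outcome, as the table shows.

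The reply does not dispose of the point. The article makes a positive, unqualified claim of blinding throughout, and describes in detail a device that defeats the claim by default unless something is done. That tests a stated property against a stated mechanism and goes beyond a missing procedural detail.

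It can also be objected that a plainer conflict matters more: the Design section says ward staff are not blinded, while the Discussion says ward doctors collected the data. That conflict is real and must be reconciled, but it is separate. Masking the watch would not resolve it, and using outside assessors would not close the route described here.

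**Conclusion.** The point holds as a risk to blinding at one visit. The assessor blinding claimed in the article is not secured at the end-of-intervention assessment, because the display reveals the arm from Day 2 and no removal or masking is described. The detection bias that could follow is limited to assessor-rated or assessor-prompted outcomes at 3 weeks or discharge. Its size cannot be calculated, since the share of assessments made with a visible watch is unknown.

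The conclusion rests on three assumptions: that the end-of-intervention battery is done in person, which the grip and walk tests require; that some of these assessments took place in wearing hours, which the Discussion makes likely but does not state; and that no masking step exists in a document not shown. If such a step exists and was followed, this route is closed.

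**What to change.** In the Data collected section, state that in both arms the unblinded person who manages the watch removes it, or switches it to the common clock page, before the assessor arrives, and that this person is not the assessor. Alternatively, state that the assessment follows the evening collection. Treat any removal interval as non-wear in both arms; the software already makes a worn or not-worn check when no movement is seen. This costs one line in the assessor instructions and a short loss of recording, at the rate shown above, which should be similar in the two arms. Switching the page or assessing after collection loses no recording.

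Describe the end-of-intervention assessment as blinded only where one of these steps was taken. The Trial status section reports recruitment ended on 16 June 2017 and final follow-up on 16 September 2017, so for this trial the remaining action is in reporting: say whether the watch was worn and visible at these assessments, for how many participants in each arm if known, and qualify the blinding claim to match. Separately, reconcile the statement that ward staff are not blinded with the statement that ward doctors collected the data.

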**Fig. 4 Fig4:**
[figure not shown]
Standard protocol items: recommendation for interventional trials (SPIRIT) figure of study timing and activities. ADL, activities of daily living; WHO, World Health Organization

The first day will serve as a baseline measure, in which none of the participants will receive feedback on their activity levels. Thereafter each morning, an investigator will provide the participant with a Smart watch to be worn on the unaffected side and will remind the participant about the purpose of the watch; either to record activity (control group) or to provide feedback on activity (intervention group). Each evening an investigator will see the person, check that there have been no unexpected events or problems such as falls, or other adverse events, and then take the watch away so that data can be downloaded, and the watch recharged for use the next day.

In order to ensure that all researchers administer the intervention in a consistent manner, we will host a series of in-service training sessions on the use of the Smart watch. These in-services will focus specifically on the setup, data storage, and output from the CHMON system.

The control group will wear the same watch, and be seen each day by the researcher to collect the watch. In this way we will control for additional attention, and to an extent for any expectations generated by involvement in a trial and wearing a watch.

#### Data collected

The assessment schedule is shown in Fig. 4. The researchers will collect the following demographic and medical information from clinical notes on admission to rehabilitation: age, sex, height, weight and dates of stroke onset and admission. Moreover at each contact the research doctors will ask the patient about any problems with the watch, and will look out for any observable adverse effects such as a skin rash. The primary data will be the daily activity counts generated by the Smart watch and downloaded daily by the researcher.

Data will be collected by investigators trained in the use of the measures, using Chinese versions of the measures where relevant. The investigator will not know which group the participant is in. The following clinical data will be collected at baseline, end of intervention or at 3 weeks, and some will be collected by phone at 3 months (see Fig. 4):The Barthel Activities of Daily Living (ADL) Index (BI) [18], a 10-item scale that assesses the ability of an individual with a neuromuscular or musculoskeletal disorder to care for him/herself.The Rivermead Mobility Index (RMI) [19], a 15-item rating scale (14-self-reported items and 1 direct observation item) that assesses functional mobility following stroke (e.g. gait, balance, and transfers).The Montreal Cognitive Assessment (MOCA) [20] (Mandarin version) [21, 22], a 16-item scale that assesses the cognitive abilities designed to detect mild cognitive dysfunction.The Fatigue Severity Scale (FSS) [23–25], a 9-item scale that measures the severity of fatigue and its effect on a person’s activities and lifestyle.The World Health Organization 12 item Disability Assessment Schedule (WHODAS) [26], a questionnaire that assesses six domains of day-to-day functioning and provides an overall disability score based on this.The Euro-QOL (EQ-5D-3L) [27, 28], a questionnaire that provides a simple measure of health for clinical and economic appraisal. This questionnaire measures the dimension of mobility, self-care, usual activities, pain/discomfort and anxiety/depression.Grip strength [29] provides a quantitative and objective measure of isometric muscular strength of the hand and forearm.The 10-m walk test (10MWT) [30] assesses walking speed over 10 m.Spatio-temporal gait features at self-selected walking speed measured during a 10MWT using an inertial sensor (LPMS-B, Life Performance Research, Japan) on the lower trunk. Participants will be instructed to walk twice along a 10-m walkway at their normal pace with a walking aid or the support of a researcher. Walking speed, cadence, step length and symmetry of spatio-temporal measures will be calculated [31].

The outcome measure on which the intervention study is powered is change in activity scores as measured by a tri-axial accelerometer from a Smart watch.

Patients with stroke tend to be discharged from in-patient rehabilitation at the Second Affiliated Hospital of Anhui University of Traditional Chinese Medicine after 2–3 weeks. Therefore, the length of the inpatient intervention phase will vary between participants but will be no more than 3 weeks. Activity score (i.e. counts) are summarised at five time points (i.e. at 2-hour increments) throughout the day. Summary analysis, from each time point and from the whole day will be used in the analysis.

#### Data handling and analysis

The data will be collected by researchers on the ward using prepared forms. The forms will be given to the research office where they will be entered into an Excel spreadsheet database. The paper forms will be stored in secure, locked files. De-identified and encrypted data will then be sent electronically on a weekly basis to Oxford Brookes University where they will be checked (a) for obvious errors (e.g. data outside the possible range) and (b) for missing data. If needed, the research centre in Hefei will be contacted to clarify apparent errors and to confirm whether missing data are truly absent. The electronic data will be stored in a secure database at Oxford Brookes University, but all investigators will have free access to all electronic data.

The following measures will be compared between the two intervention groups: Barthel ADL index, Rivermead Mobility Index, Fatigue Severity Scale, Montreal Cognitive Assessment, WHO Disability Assessment Scale, EuroQol 5D-5L, and length of inpatient stay. Data will be analysed based on the intention-to-treat principle.

Descriptive statistics will be calculated for demographic characteristics and compliance data. The independent samples or the chi-square (X^2^) test will be used to assess differences between group means and frequencies at baseline, the test being chosen according to data type. Measures that differ significantly between the two groups will be included as covariates in statistical models comparing interventions. The distribution of data will be analysed.

SPSS v23 will be used to investigate progression within groups by regression analysis. The frequency that each person achieves their activity goal, as set automatically by the watch, will be explored within the intervention groups at discharge from inpatient rehabilitation.

For outcome data, the linear mixed models (LMM) procedure in SAS 9.4 will be used to determine the mean changes in measures, as response variables, according to two intervention regimes (intervention and control) and three repeated measurements, using baseline as a covariate. Distribution of the data will be checked according to various methods of analysis, which are employed at different stages of the study. The analysis of outcome, which will be based on LMM, assumes a Gaussian distribution that can be checked and tested by standard methods. However, we also note that LMM is, in general, quite robust to violation of the distributional assumptions.

This model treats all factors as categorical, and so different types of data can be used. Further and based on the differences in least squares (marginal) means between the two groups (intervention vs control), provided by LMM analysis, power, effect size (Cohen’s d) and their 95% non-central confidence limits will be calculated. Analysis will be used for each outcome measure. The “group” term is the intervention group; the “time” term is the assessment time point. The group-by-time interaction effect will reveal if there is a greater change over time in one group compared with the other.

For a sample size estimate, we used a conservative estimate of the standardised effect size of change in physical activity levels from the initial assessment to discharge from inpatient rehabilitation (i.e. the first phase of the study) as our primary outcome of interest. Our pilot work suggests an effect size of 0.12, and for alpha 0.05 and power 0.95 for repeated measures with three measurement points, we expect a sample of 182 to be adequately powered. From pilot work we expect 10% to drop out, and so we propose to recruit 200 patients.

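### Baseline significance tests between randomised arms select the extra covariates; this costs precision and tends to leave out the walking-speed stratum

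*Protocol article*

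**What the plan says.** Allocation is random: "Participants will be randomly assigned to one of two groups" (Protocol article, Design, after Fig. 1). The same part of the article says: "A block stratified randomization approach with two strata will be used, based on walking speed at the time of recruitment". The cut is at 0.42 m/s.

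Under Data handling and analysis, an independent-samples or chi-square test "will be used to assess differences between group means and frequencies at baseline, the test being chosen according to data type". The rule follows directly: "Measures that differ significantly between the two groups will be included as covariates in statistical models comparing interventions". The level of these tests is not given, and the set of measures to be tested is not listed.

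The same section then describes a linear mixed model with two groups and "three repeated measurements, using baseline as a covariate". So one covariate, the baseline value, is fixed whatever the tests show. The walking-speed stratum is not named as a covariate. That silence alone could be left to an analysis plan, but the selection rule is stated outright.

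**The concern.** With sound randomisation the null hypothesis of a baseline test is true by construction, so a significant result marks an unusual draw and nothing more. What makes a covariate worth having is how strongly it predicts the outcome, and the p-value between arms does not measure that. The rule can admit a weak predictor that happens to differ. It can also leave out a strong predictor whose imbalance falls short of significance.

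Walking speed shows the problem. Stratified randomisation is there to balance it, so it is less likely than other measures to differ significantly. The rule therefore tends to exclude the one factor that the design singled out.

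At stake are the precision of the treatment estimate, the accuracy of its standard error, and whether the full covariate list can be written down before data by arm have been examined.

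**Working it through.** **1. The plan's own figure.** The only related figure is the sample size, used here to set the simulation. Inputs from Data handling and analysis: effect size 0.12 (read as Cohen's f), alpha 0.05, power 0.95, three measurements. Assumed, because not stated: within-person correlation 0.5 and sphericity. For the group-by-time interaction, λ = f²·N·m/(1−ρ) = 0.0144 × 182 × 3 / 0.5 = 15.72, with 2 and 360 degrees of freedom. Power is 0.952. The smallest N is 181, or 182 with equal arms, so the stated 182 reproduces. The covariate rule does not enter this calculation.

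**2. Candidate measures.** Data collected lists "age, sex, height, weight and dates of stroke onset and admission". With the two dates combined as time from stroke to admission, that is 5. It then says: "The following clinical data will be collected at baseline, end of intervention or at 3 weeks". The clinical list gives 8 more: Barthel, Rivermead, cognition, fatigue, WHODAS, EuroQol, grip strength and 10-m walk. The total is 13, or up to 17 with four gait features. Day-1 activity is not counted, because it is the baseline of the primary outcome and is already in the model.

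**3. Chance that at least one enters.** With tests at an assumed 0.05 and independent measures, P = 1 − 0.95^k.
- k = 5: 1 − 0.774 = 0.226
- k = 13: 1 − 0.513 = 0.487
- k = 17: 1 − 0.418 = 0.582

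The measures overlap, so independence gives the upper end. With a correlation of 0.3 between every pair, simulation gave 0.41–0.43 for 13 measures and 0.19–0.22 for 5.

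**4. What the rule does to the test.** Simulation with 182 patients, 1:1, one outcome, a linear model and 13 measures correlated at 0.3. There were 6,000 null runs (Monte Carlo SE about √(0.05 × 0.95/6000) = 0.003) and 3,000 runs with an effect of 0.48 SD (about √(0.9 × 0.1/3000) = 0.005). The variance explained and the effect are assumptions.

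| Variance explained by the measures | Type I error: rule | Type I error: fixed set | Power: no added covariates | Power: rule | Power: fixed set |
|---|---|---|---|---|---|
| 10% | 0.051 | 0.054 | 0.898 | 0.905 | 0.903 |
| 30% | 0.037 | 0.048 | 0.897 | 0.923 | 0.962 |
| 50% | 0.032 | 0.045 | 0.905 | 0.948 | 0.996 |

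The fixed set here is all 13 measures. A single covariate is closer to a short list. When it explained 10%, 30% and 50% of variance, power was 0.897, 0.912 and 0.913 with the rule, against 0.917, 0.967 and 0.994 when it was always included.

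Over all settings run (1, 5 and 13 measures), type I error was 0.032–0.051 with the rule and 0.044–0.054 with fixed covariates.

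**5. Why the test becomes conservative.** The rule removes the largest chance imbalances, so the estimate varies less, but the reported standard error hardly falls. With 13 measures explaining 50%, the true SD of the estimate was 0.129 and the mean reported standard error 0.142. The ratio 0.142/0.129 is 1.10, so the standard error was about 10% too large.

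**The case against.** The strongest defence is that the core of the model is already fixed. Group, time, their interaction and the outcome's baseline are all specified, and the rest of the rule is mechanical, with little room to pick covariates by their effect on the result. This stands, and it limits the point to the added covariates. A reader might infer that chance decides the whole treatment comparison, or that the rule invites selective analysis. The text supports neither.

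The entry probability also needs restraint. The level is not stated, the measures overlap, and the paragraph can be read as testing only demographic items. A reader might take away that more than half of such trials would have their model altered by chance. That needs more measures than the 13 counted here, together with independence. In addition, a covariate entering the model does not mean that the conclusion changes.

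Third, no harm to error rates was found. A reader might expect data-driven selection to inflate false positives. In these simulations it did not, and the rule matched or slightly exceeded the power of adding no covariates at all. The loss is only against a fixed set, and it disappears when 13 measures together explain 10% of variance. The documents give no prognostic strength for any measure beyond the outcome's own baseline, so the true loss is unknown.

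None of this supplies a reason for the rule. It shows that the damage is limited.

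**Conclusion.** The point holds in a limited form and should be fixed. The plan states a rule that selects additional covariates by chance imbalance rather than prognostic value, and that tends to pass over the stratification factor. Assuming 0.05 tests, at least one covariate would enter by chance in about 41–49% of trials for 13 measures, and in 23% for the five demographic and medical items if independent.

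The consequence is a nominal-to-conservative test and some lost precision. With 13 measures, the power difference from a fixed set ranged from none (0.905 against 0.903) to about 5 percentage points (0.948 against 0.996), depending on how prognostic the measures are. These figures rest on the assumed test level, correlation, variance explained and 0.48 SD effect, and on a single-outcome linear model in place of the full mixed model. They do not support a claim of bias or of inflated type I error.

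**What to change.** Delete the test-and-include rule under Data handling and analysis. Replace it with a fixed list for every treatment comparison: the outcome's baseline value (already specified) and the walking-speed stratum used in randomisation. A short prognostic list from data already collected, such as age and time since stroke, may be added on clinical grounds. Present baseline data by arm descriptively, without tests. Keep any adjustment prompted by observed imbalance as a labelled sensitivity analysis.

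The cost is a changed sentence and one or two degrees of freedom, or slightly more with the optional list. No new data or patients are needed, and the 182 is unaffected. The Trial status section puts final follow-up in September 2017, and investigators have open access to the electronic data. The change should therefore be dated and should say whether the arms had already been compared. If they had, report the fixed model as primary and disclose the change.
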